## Exclusion criteria

A potential subject who meets any of the following criteria will be excluded from participation in this study:

- cT4b/multivisceral resection;
- cTNM stage 4 (M1);
- ASA 4;
- Immune modulating medication;
- Prior midline or transverse laparotomy larger than 10 cm (not including Pfannenstiel and McBurney's incision);
- Perforated disease/peritumoral abscess/fistula;
- Acute obstruction;
- Emergency surgery;
- Neuroendocrine neoplasm (NEN);
- Other primary malignancy treated within 5 years from diagnosis of colon cancer, except for curatively treated prostate, breast, skin and cervical cancer.

## Sample size calculation

Sample size calculation is performed with the aim to demonstrate safety with non-inferiority for the primary endpoint overall 90-day morbidity. If there is truly no difference between the standard and experimental treatment, then 1095 patients (365 patient in each of the three groups) are required to be 80% sure that the lower limit of a one-sided 95% confidence interval (or equivalently a 90% two-sided confidence interval) will be above the non-inferiority limit of 7%. Therefore, in the one group 365 patients will be included (control group) and in the other group 730 patients will be included (implementation and consolidation phase together).

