# STUDY DESIGN

The design of this trial is a multicenter prospective interventional sequential cohort study with a transition period in which implementation of the standardized technique is performed in the same centers after education and hands on training. Proctoring of the new technique will be provided during implementation. The second data evaluation of the clinical and oncological outcomes of the consecutive patient group will be collected in the group of patients after proctoring is finished, the so called consolidation phase. This study is primarily designed as a non-inferiority trial, based on short-term postoperative complications, with the aim of ultimate improvement of long-term oncological outcome. The accrual of both the control patients and the patients after implementation will be within the national Prospective Dutch ColoRectal Cancer cohort (PLCRC) with additional video analysis and image collection with additional informed consent. The primary endpoint is safety during implementation of a new technique. This is measured by 90-day morbidity with the Clavien-Dindo classification [15]. The assumption is that the perioperative morbidity (26% 30-day overall postoperative complication rate; as earlier published based on the DCRA database [16]) will not be increased by implementation of the new standardized technique with a non-inferiority margin of 7%, therefore not exceeding 33%.

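### The non-inferiority criterion for 90-day morbidity is written in the wrong direction: it asks for a lower confidence limit above 7%, when safety requires an upper limit below +7 points

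*Protocol*

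**What the plan says.** Section 6.4 sizes the trial to "demonstrate safety with non-inferiority for the primary endpoint overall 90-day morbidity". It assumes "If there is truly no difference between the standard and experimental treatment" and gives a total of 1095 patients, 365 control and 730 in the implementation and consolidation phases together, who "are required to be 80% sure" of success. Success is worded as follows: "the lower limit of a one-sided 95% confidence interval (or equivalently a 90% two-sided confidence interval) will be above the non-inferiority limit of 7" percent. The limit carries no minus sign, and the section does not say which group is subtracted from which.

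Section 5 (Study design) gives the margin and its direction. Starting from a "26% 30-day overall postoperative complication rate", morbidity "will not be increased by implementation of the new standardized technique with a non-inferiority margin of 7%, therefore not exceeding 33" percent. Section 4.3 (Hypothesis) likewise expects the technique to be safe, with no rise in 90-day morbidity.

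Section 10 (Statistical analysis) describes chi-square tests, regression models and a 0.05 significance level. It contains no confidence-interval criterion for the primary endpoint.

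**The concern.** For an adverse outcome with a margin expressed as an allowed increase, the new technique is non-inferior when the data rule out an increase as large as the margin. That is a statement about the upper confidence limit of new minus control. Section 6.4 refers instead to the lower limit and requires it to exceed a positive 7%. That form belongs to a success endpoint, and there the limit would be minus 7%.

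The sentence is the only confidence-interval criterion the protocol gives for its primary, safety endpoint, in a study that changes surgical technique in more than 40 centres. If an analysis plan or report copies it, the stated criterion would either reward harm or be practically unattainable for a safe technique.

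**Working it through.** **Inputs.** Control rate 26% and margin 7 points (section 5). True difference zero, power 80%, one-sided 5% level, 365 control and 730 experimental patients (section 6.4). Normal approximation with unpooled variance. z(0.95) = 1.645, z(0.80) = 0.842.

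**1. Reproduce the plan's sample size under the correctly directed rule.** With 1:2 allocation,

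n(control) = (1.645 + 0.842)² × 0.26 × 0.74 × (1 + 1/2) / 0.07² ≈ 364.1, rounded up to 365.

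The experimental group is 2 × 365 = 730 and the total is 1095, an exact match. The alternatives tried do not match: 1:1 allocation gives 486 per group, and a one-sided 2.5% level at 1:2 gives 463 controls.

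**2. Precision.**

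SE = √[0.26 × 0.74 × (1/365 + 1/730)] = 0.0281, or 2.81 points.

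One-sided 95% half-width = 1.645 × 0.0281 = 0.0463, or 4.63 points.

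**3. Observed difference each rule needs** (SE at 26% in both groups).

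- Correct rule, upper limit of new minus control below +7: an observed excess below 7 − 4.63 = 2.37 points.
- Written rule, lower limit above +7: an observed difference above 7 + 4.63 = 11.63 points, in whichever direction the subtraction is made.

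**4. Probability of meeting each rule with no true difference.**

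- Correct rule: Φ(0.07/0.0281 − 1.645) = 0.801.
- Written rule: 1 − Φ(0.07/0.0281 + 1.645) = 0.000018, for either direction of subtraction.

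**5. Probability under other true differences** (SE recalculated with control at 26% and the new rate at 26% plus the difference).

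| True new minus control | Written rule, new minus control | Written rule, control minus new | Correct rule |
| --- | --- | --- | --- |
| −7 points | <0.001 | 0.050 | >0.999 |
| 0 | 0.000018 | 0.000018 | 0.801 |
| +7 points | 0.050 | <0.001 | 0.050 |
| +14 points | 0.773 | <0.001 | <0.001 |
| +15 points | 0.861 | <0.001 | <0.001 |

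Read as new minus control, the written rule becomes easier to meet as harm grows. Read as control minus new, it is a test of superiority by more than 7 points, met only 5% of the time even if morbidity truly falls by 7 points. Taking complication-free rates, new minus control, gives that same superiority test.

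**6. Would a minus sign alone repair it?** No. If the difference is new minus control in morbidity, a lower limit above −7 would be met with probability about 0.999 at a true rise of 7 points. The direction of the difference has to be stated as well.

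**The case against.** The strongest reply is that the intent is clear. Section 5 has the direction right, with a 33% ceiling, and section 4.3 agrees. The sample size was evidently calculated for the proper rule, and the 80% in the sentence itself fits only that rule, so a careful reader can spot the slip. The sentence sits in the sample size section, and the operational test may be set out in an analysis plan that is not at hand. The fault could also be described more narrowly: with control minus new, or complication-free rates, and a limit of −7%, the phrase about a lower limit lying above the limit would be standard.

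Much of this stands. An analyst who read sections 4.3 and 5 would probably apply the right rule, so the probabilities above describe the sentence taken literally and do not forecast what the trial team would do. It does not rescue the sentence, however. The document gives neither the minus sign nor the direction of the difference, and section 10 offers no correct version. The contradiction between sections 5 and 6.4 exists whatever an analysis plan may say.

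**Conclusion.** The concern holds. The criterion in section 6.4 is not a non-inferiority criterion under any direction of the difference, and it contradicts sections 4.3 and 5. Under the plan's own assumption of no difference, it would be met about 2 times in 100,000, where the same sentence promises 80 in 100. The error is confined to the wording: the margin, the power and the total of 1095 are mutually consistent once the rule is turned round.

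The figures assume a true control rate of 26%, the normal approximation, independent patients and the full 365 and 730 analysed. The direction of the error depends on none of these. The 26% is a 30-day rate used for a 90-day endpoint; that is a separate matter and does not affect this conclusion.

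**What to change.** Rewrite the criterion in section 6.4 along these lines: there is 80% power for the upper limit of the one-sided 95% confidence interval (the upper end of the two-sided 90% interval) for the difference in 90-day morbidity, standardised technique minus control, to fall below +7 percentage points.

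Name the order of subtraction explicitly, and use the same statement wherever the primary criterion is repeated, including any analysis plan. The cost is one sentence. The group sizes of 365 and 730, the margin and the power are unchanged.

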   3. Prospective inclusion of consecutive patients undergoing laparoscopic right hemicolectomy in the participating hospitals in three months.
2. **Delphi phase**: Development of Standard Laparoscopic Right Hemicolectomy: an (inter)national Delphi study
   1. Approaching specialists to participate in the Delphi method (from participating hospitals in step 1).
   2. Identification of crucial steps and measures according to literature and expert’s opinion (Delphi method).
   3. Documentation of steps and the order in which they need to be performed, development of a competency assessment tool (CAT).
3. **Training phase**: Skills center training facility
   1. Training the participating surgeons in the method of the standardized laparoscopic right hemicolectomy, as consented in the Delphi method.
4. **Implementation phase**: implementing the standardized laparoscopic right hemicolectomy with proctoring during another period with prospective inclusion of 365 consecutive patients (total duration of inclusion is 4 months, possibility to extend until maximum of 6 months). N=40+ centers; N=365 videos.
5. **Consolidation phase**: Collection of a third group of 365 consecutive patients with collection of surgical videos in all participating hospitals (total duration of inclusion is 4 months, possibility to extend until maximum of 6 months). N=40+ centers; N=365 videos.
   1. Rating videos.
   2. Comparing with pre-implementation performance based on outcome measures reflecting oncological quality of surgery, and 90-day clinical outcomes.
   3. Comparing with pre-implementation performance based on the long-term outcomes. (3-year DFS and 5-year OS).

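### The sample size pools implementation and consolidation (365 vs 730), but sections 5 and 8.2 attach the clinical comparison to consolidation alone, where power is about 70%, not 80%

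*Protocol*

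**What the plan says.** - **Section 6.4 (Sample size calculation)** asks for 1095 patients in three groups of 365. The control group is one side of the comparison, and "in the other group 730 patients will be included (implementation and consolidation phase together").
- **Section 5 (Study design)** describes a second evaluation of clinical and oncological outcomes that "will be collected in the group of patients after proctoring is finished, the so called consolidation phase". On its wording, the proctored patients are outside that evaluation. The same section also states: "The primary endpoint is safety during implementation of a new technique".
- **Section 8.2 (Study procedures)** gives comparison with the pre-implementation period as the purpose of the third group. In the five-step list, "Comparing with pre-implementation performance based on outcome measures reflecting oncological quality of surgery, and 90-day clinical outcomes" appears under step 5 (Consolidation phase). Step 4 (Implementation phase) lists no comparison.
- **Section 10 (Statistical analysis)** names tests but no comparison groups for the primary endpoint.

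**The concern.** Section 6.4 uses one experimental group (730 patients, both later phases). Sections 5 and 8.2 point to another (365 patients, consolidation only). The choice matters in two ways.

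First, it sets the power. The 80% in section 6.4 was computed for the pooled group and does not carry over to a comparison with half as many experimental patients.

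Second, it sets what can be concluded. The trial is presented as a check on safety while the technique is being introduced, and section 3 cites evidence that learning curves can raise complication rates. In the pooled group the proctored phase carries half the weight, so a good consolidation phase can offset a poor implementation phase. The cohorts are sequential and not randomised. If the text leaves the contrast open, it could be settled after some cohorts' results are known.

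**Working it through.** **Inputs, all from the protocol**
- Planning rate 0.26 in both groups: section 5, "26% 30-day overall postoperative complication rate"; section 6.4, "If there is truly no difference between the standard and experimental treatment".
- Margin 0.07 absolute: section 5, "with a non-inferiority margin of 7%, therefore not exceeding 33" percent.
- One-sided 5%: section 6.4, "one-sided 95% confidence interval (or equivalently a 90% two-sided confidence interval"), so z = 1.645.
- Power 80%, so z = 0.842.
- Three groups of 365: section 6.4.

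**Step 1: reproduce the stated size.** With r experimental patients per control,

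n(control) = (1.645 + 0.842)² × 0.26 × 0.74 × (1 + 1/r) / 0.07²

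- r = 2: about 364.1, rounded up to 365 controls and 730 others, 1095 in total. This is the protocol's figure.
- r = 1: about 485.5, so 486 per group.

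The stated size therefore comes from the pooled 1:2 contrast.

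**Step 2: power of each contrast with no true difference.** Power = Φ(0.07/SE − 1.645), with SE = √[0.26 × 0.74 × (1/n₁ + 1/n₂)].

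| Contrast | n | SE | Power |
|---|---|---|---|
| Control vs pooled | 365 vs 730 | 0.0281 | 80.1% |
| Control vs consolidation | 365 vs 365 | 0.0325 | 69.5% |
| Control vs implementation | 365 vs 365 | 0.0325 | 69.5% |

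Exact binomial power of the same interval is 80.6% (pooled) and 69.5% (single phase). The Farrington-Manning method gives 81.4% and 69.5%.

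**Step 3: sensitivity to the planning rate.** The 26% is a 30-day rate and the endpoint runs to 90 days, so the true rate may differ. Over an assumed range of 20% to 40%, power for a single-phase contrast falls from 76.4% to 61.2%, and for the pooled contrast from 86.1% to 72.0%. The single-phase contrast is below 80% throughout.

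**Step 4: dilution under pooling.** The protocol gives no phase-specific effects, so this scenario is an assumption: control 26%, implementation 33% (exactly at the margin), consolidation 26%.
- Pooled true difference: (0.07 + 0)/2 = 0.035.
- Variance: 0.26 × 0.74/365 + (0.33 × 0.67 + 0.26 × 0.74)/(4 × 365) = 0.000527 + 0.000283 = 0.000810, so SE = 0.0285.
- P(non-inferiority declared) = Φ((0.07 − 0.035)/0.0285 − 1.645) = Φ(−0.415), about 34%.

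An implementation-only test in this scenario would pass 5% of the time, by construction.

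**The case against.** The strongest reply is that section 6.4 is the only place that ties the primary test to named groups, and it does so explicitly. Sections 5 and 8.2 never use the words primary comparison. Step 5 of section 8.2 may simply list end-of-study tasks: it also includes rating the videos, which are collected in steps 1, 4 and 5. The last objective in section 4.2 compares the cohort after training with the cohort before it. Both later phases follow training, so that fits the pooled reading. On this view the plan needs no more than a cross-reference.

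Much of this stands, and it limits the point in several ways.
- A reader might infer three rival primary contrasts, the third being implementation alone, from the sentence on safety during implementation. That sentence names no groups and can cover the whole roll-out. It is a rationale, not a contrast. The conflict is between section 6.4 and sections 5 and 8.2.
- A reader might infer that the 80% is miscalculated. It is not. The protocol claims it for 365 vs 730, and it reproduces.
- A reader might infer that the implementation phase is expected to do harm. The documents give no phase-specific effects. The scenario in step 4 shows what pooling permits, not what is likely.

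What does not fall away is the wording of section 5, which places the evaluation of clinical outcomes after proctoring has ended, and the stated purpose of the third group in section 8.2. The primary endpoint is itself a 90-day clinical outcome, so both bear on it, and section 10 does not resolve the difference. If the pooled reading is right, those two sections need correcting.

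**Conclusion.** The point holds as an inconsistency over which patients form the experimental group for the 90-day comparison. Section 6.4 pools both later phases, while sections 5 and 8.2 assign the comparison to consolidation. The stated 80% power applies to the pooled contrast only (80.1%). For control vs consolidation it is 69.5%, so the chance of missing non-inferiority when there is no difference rises from about 20% to about 30%. These figures rest on 26% in both groups, a 7-point margin and one-sided 5%. A higher 90-day rate would lower both powers.

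The pooled result alone is also an incomplete answer to the stated aim of safety during implementation. In the assumed case of step 4 it passes about one time in three with the proctored phase at the margin. That supports showing the phases separately. It does not show that the pooled test is invalid for the pooled question.

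**What to change.** 1. Name one primary contrast, in the same words, in sections 5, 6.4, 8.2 and 10. Pooled implementation plus consolidation (730) vs control (365) is the one that matches the sample size and keeps the stated 80%.
2. If control vs consolidation is what the sponsor intends, restate the power in section 6.4 as about 70%. Reaching 80% would need 486 per group in that comparison, which is 486 − 365 = 121 more in each.
3. Pre-specify the implementation-only and consolidation-only risk differences against control, each with a 90% confidence interval set against the +7-point margin, as supporting results beside the pooled one. State that each has about 70% power under the planning assumptions.

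The supporting results should not become a second pass/fail requirement. With no true difference, an implementation-only criterion would fail about 30% of the time, so the overall claim would have at most about 70% power. A ban on particular reporting phrases is not needed either.

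The cost of items 1 and 3 is protocol wording, two additional estimates and a less favourable stated power for the single-phase comparisons. No patients are added if the pooled contrast remains primary.

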# TREATMENT OF SUBJECTS

## Investigational treatment

The implementation of the standardized laparoscopic right hemicolectomy with proctoring with prospective inclusion of consecutive patients with collection of surgical videos in all participating hospitals will be investigated. This method will be compared with the laparoscopic right hemicolectomy performed by the same hospitals before the training and implementation of the standardized technique. The clinical outcomes will be collected using the DCRA database and the oncological outcomes will be collected by the surgeons, surgical registrars and/or trained research nurses in the participating centers.

# METHODS

## Study parameters/endpoints

### Main study parameter/endpoint

The primary endpoint is the 90-day morbidity with Clavien-Dindo classification.

### Secondary study parameters/endpoints

- Intraoperative complications (i.e. vascular injury, injury to other organs);
- 90-day mortality;
- Conversion;
- Operative time;
- Blood loss;
- Validated assessment of plane of dissection;
- Validated assessment of level of vascular ligation;
- Grading of the resection specimen according to Benz et al. [17];
- Total lymph node count;
- Number of resected positive lymph nodes;
- Resection margins;
- Completeness of mesocolic excision based on postoperative CT imaging;
- Locoregional recurrence;
- Distant metastasis;
- 3-year disease free survival (DFS);
- 5-year overall survival (OS);
- Long-term morbidity: incisional hernia, adhesion related small bowel obstruction, readmissions, reinterventions, anastomotic leakage.

## Study procedures

First the variability of surgical techniques amongst surgeons and centers for right-sided colon cancer will be evaluated by a 4 months period (possibility to extend until maximum of 6 months) prospective inclusion of 365 patients and evaluating preoperative CT imaging, full length surgical video and clinicopathological outcomes, as well as the CT imaging one year post-operatively as routine part of oncological follow-up.

Second, a Delphi method amongst participating colorectal surgeons will be applied after the 4 months period (possibility to extend until maximum of 6 months) of video collection, to establish a detailed standardized technique for laparoscopic right hemicolectomy for colon cancer. This technique will include essential elements that can potentially improve outcomes such as approach, number and positioning of trocars, plane of retroperitoneal dissection, level of vascular ligation with extent of vertical lymphadenectomy, technique for constructing the anastomosis and preferred extraction site.

Third, the standardized technique will be taught during hands-on surgical training.

Fourth, the new technique will be implemented in a controlled fashion with proctoring in the same centers, with another 4 months period (possibility to extend until maximum of 6 months) of prospective inclusion of 365 patients.

Finally, a third consecutive group of patients will be included to consolidate the standardized technique after the learning curve. The same preoperative CT imaging, full length surgical videos and clinicopathological outcomes as well as the CT imaging one year post surgery will be collected and analyzed, in order to be able to compare the performance with the pre-implementation period. Again, 365 patients will be prospectively included in a 4 months period (possibility to extend until maximum of 6 months).

Schematic five step approach:

[figure not shown]

1. **Control cohort phase**: Prospective mapping of current practice with surgical variations in laparoscopic right hemicolectomy (total duration of inclusion 4 months, possibility to extend until maximum of 6 months). N=40+ centers; N=365 videos
   1. METC approval for the use of anonymized videos of a laparoscopic procedure and collection of corresponding clinical outcomes.
   2. Approaching hospitals for participation (high volume centers (50+ colon cancers).
   3. Prospective inclusion of consecutive patients undergoing laparoscopic right hemicolectomy in the participating hospitals in three months.
2. **Delphi phase**: Development of Standard Laparoscopic Right Hemicolectomy: an (inter)national Delphi study
   1. Approaching specialists to participate in the Delphi method (from participating hospitals in step 1).
   2. Identification of crucial steps and measures according to literature and expert’s opinion (Delphi method).
   3. Documentation of steps and the order in which they need to be performed, development of a competency assessment tool (CAT).
3. **Training phase**: Skills center training facility
   1. Training the participating surgeons in the method of the standardized laparoscopic right hemicolectomy, as consented in the Delphi method.
4. **Implementation phase**: implementing the standardized laparoscopic right hemicolectomy with proctoring during another period with prospective inclusion of 365 consecutive patients (total duration of inclusion is 4 months, possibility to extend until maximum of 6 months). N=40+ centers; N=365 videos.
5. **Consolidation phase**: Collection of a third group of 365 consecutive patients with collection of surgical videos in all participating hospitals (total duration of inclusion is 4 months, possibility to extend until maximum of 6 months). N=40+ centers; N=365 videos.
   1. Rating videos.
   2. Comparing with pre-implementation performance based on outcome measures reflecting oncological quality of surgery, and 90-day clinical outcomes.
   3. Comparing with pre-implementation performance based on the long-term outcomes. (3-year DFS and 5-year OS).

